## I. STUDY ABBREVIATIONS AND BRIEF DEFINITIONS

CWT – Community-wide treatment

Hb – Hemoglobin

Epg – eggs per gram

GEE - Generalized estimating equations

ICC – intra-class correlation

MDA – Mass drug administration delivered on an annual basis at a target dose of 40 mg/kg, with dose estimated from subject height using a dosing pole

SAC – School age children

SBT – School-based treatment

Sh – *Schistosoma haematobium*

Sh1 – Sh studies of Sustaining control, in communities found to have prevalence <25% among 13-14 year-old children during eligibility screening

Sh2 – Sh studies of Gaining control, conducted in communities found to have prevalence  $\geq$ 25% among 13-14 year-old children during eligibility screening

SCORE — Schistosomiasis Consortium for Operational Research and Evaluation

Sm – *Schistosoma mansoni*

Sm1 – Sm studies of Sustaining control, conducted in communities found to have prevalence <25% among 13-14 year-old children during eligibility screening

Sm2 – Sm studies of Gaining control, in communities found to have prevalence  $\geq 25\%$  among 13-14 year-old children during eligibility screening

SUDS – SCORE Uniform Data Set

Y – Year: Y1 data collection is defined as the baseline data collection, which occurs before treatment. Y1 treatment refers to the first MDA treatment

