#### d. Study design: Cohort studies of *Schistosoma*-associated morbidity

**Overview:** The Cohort studies are sub-studies within SCORE Gaining Control studies, i.e., in communities with  $\geq 25\%$  prevalence of schistosomiasis during eligibility testing. They involve only Arms 1 and 6 of the Gaining Control studies, selected to represent the most intensive and a much less intensive intervention sequence, respectively (see below). Enrolled children were followed for five years, with evaluation occurring at Years 1 (baseline), 3 (after two MDA treatments), and 5 (after four MDA treatments).

**Cohort study design and expected sample size:** Cohort studies aimed to enroll 100 children from at least 4 communities/villages in each study arm, for a total of 800 children per study. The two Sh2 cohorts were discontinued: Mozambique because of significant loss to follow-up and Niger because of inappropriate randomization.

| Cohort Study | Year 1 | Year 2 | Year 3 | Year 4 |
|--------------|--------|--------|--------|--------|
|--------------|--------|--------|--------|--------|

[figure not shown]

Villages for inclusion in this study were meant to be a random sample of all the villages in the two study arms of interest (Arms 1 and 6); however, to facilitate the survey work investigators were allowed to select them randomly from among a restricted group of no less than 10 out of the 25 villages in each arm, chosen, for example, to exclude very remote villages.

The protocol called for selecting the 100-child cohort from the school class that starts at 7 or 8 years of age. If there were over 100 children in this class, children were to be randomly selected for participation. If this class did not include 100 children, then all of the children in that class should have been enrolled along with a random selection of children in the next older class, in order to reach the total of 100 study subjects.

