## b. Individual-level data in Cohort studies

**Primary Morbidity Markers:** The following were measured in Years 1, 3, and 5, except for ultrasound, which was to be conducted in Years 1 and 5. Kenya chose to perform abdominal ultrasounds in Year 3 as well. All the markers will be available in the SCORE uniform datasets (SUDS) as described in section IV. For details on variable coding, please refer to Appendix F of this SAP: 'Data Dictionary for SCORE Cohort Studies.'

1. Height in cm and weight in kg transformed to age-adjusted Z-scores for each outcome using established WHO/CDC standards, and presence or absence of stunting or wasting.
2. Blood hemoglobin (Hb). While collection of a venous sample was preferred, finger prick capillary blood was acceptable. Based on WHO criteria, at sea level and up to 1000m elevation, anemia is defined as Hb < 11.5 g/dL for age < 12 years, Hb < 12 for females > 12 years, Hb < 12 for males 12-15, and Hb < 13 for males > 15. Altitude-related changes in normal circulating hemoglobin levels require adjustment of anemia cutoffs for higher elevations. The cutoffs are 0.2 gm/dL higher for each age group in Tanzania and Kenya locations as they are located at 1000-1250m elevation [1].
3. Physical fitness (VO2) based on the 20-meter shuttle run protocol. VO2 is calculated as follows:
  - (1) Speed =  $8 + .5 \times \text{No. shuttles successfully completed}$ ;
  - (2)  $\text{VO2} = 31.025 + 3.238 \times \text{Speed} - 3.248 \times \text{Age in years} + .1536 \times \text{Speed} \times \text{Age in years}$ .
4. Measures of well-being based on the standardized questionnaire, PedsQL. This instrument was translated and validated prior to local use. The Physical and other subscale scores for PedsQL were based on child's graded responses to each question. Scale scores were calculated by 1) reversing item answer scores and linearly transforming to a 0-100 scale [0=100, 1=75, 2=50, 3=25, 4=0], and 2) for each subscale, adding transformed scores and dividing by number of items scored. If over 50% of items in the subscale are missing, the subscale is coded as missing. C in the variable name indicates child responses, P indicates parent.
5. Abdominal ultrasound in Years 1 and 5. (Detailed information on variable coding can be found in Appendix F.)

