## VII. STUDY QUESTIONS AND END-POINTS OF INTEREST FOR COHORT STUDIES

### a. Key research questions

The primary research questions in the cohort studies relate to comparisons of outcome measures between arms at Year 5, and the change from baseline and follow-up, by arm. The primary research questions are:

- 1a. Do morbidity markers among cohort children at Year 5 differ by study arm?
- 1b. How do changes in morbidity markers among cohort children from baseline to follow-up differ by arm?

Interpretation of the results of these analyses needs to be done in the context of the data on prevalence and intensity in the two arms. If data are available on malaria and other factors that could affect morbidity findings, these should be evaluated as well.

Further exploratory analysis should evaluate differences in morbidity by infection intensity. For example, in any given year, is there a relationship between intensity and morbidity measurements? Is there a relationship between changes in individual's intensity over time and changes in their morbidity measures? Note that some outcomes (e.g., liver pattern C) should be assessed taking cumulative exposure into account, whereas others are more likely to be related to contemporaneous exposure.

SCORE is committed to ensuring that the link between intensity and morbidity outcomes is evaluated. However, this is beyond the scope of the core SAP.

The original statistical analysis plans for evaluating the Cohort studies is found in Appendix J.

The following outcomes are of primary interest:

- 1.a. Height and/or weight, as calculated using WHO/CDC age-standardized Z-scores for height (HAZ), weight (WAZ) and body mass index (BAZ); these are typically treated as continuous outcomes.
- 1.b. Growth stunting (HAZ < -2) or nutritional wasting (BAZ < -2) as categorical outcomes.
- 2.a. Hb levels (continuous).

- 2.b. Anemia (categorical). Based on WHO criteria, anemia is defined as Hb < 11.5 g/dL for age < 12 years, Hb < 12 for females > 12 years, Hb < 12 for males 12-15, and Hb < 13 for males > 15. Altitude-related changes in normal circulating hemoglobin levels require adjustment of anemia cutoffs for higher elevations. The cutoffs are 0.2 gm/dL higher for each age group in Tanzania and Kenya locations as they are located at 1000-1250m elevation [1]
3. Maximum oxygen uptake, VO2 max (continuous) estimated based on shuttle run scores.

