| (CI)                          |  |  |  |  |  |  |
| Mean hemoglobin in gm/dL (SD) |  |  |  |  |  |  |
| Prevalence of anemia % (CI)   |  |  |  |  |  |  |
| Mean Vo2 max score (SD)       |  |  |  |  |  |  |
| Mean PedsQL score (SD)        |  |  |  |  |  |  |
| Total Score                   |  |  |  |  |  |  |
| Physical                      |  |  |  |  |  |  |
| Emotional                     |  |  |  |  |  |  |
| Social                        |  |  |  |  |  |  |
| School                        |  |  |  |  |  |  |
| Liver pattern                 |  |  |  |  |  |  |
| B % (CI)                      |  |  |  |  |  |  |
| C or higher % (CI)            |  |  |  |  |  |  |

Tables 4 (multiple tables). Comparison between Arm 1 and Arm 6 of Year 5 morbidity outcomes.

For each outcome, the following type of table should be developed. The results should be as indicated in the cells below.

Example: Table 4A. Unadjusted and adjusted models for **anemia** at Year 5.

|                     | Unadjusted                   | Adjusted                   |
|---------------------|------------------------------|----------------------------|
| Arm (1 vs 6) | Parameter of Interest** (CI) | Parameter of Interest (CI) |
| Age          | ---                          | Parameter of Interest (CI) |
| Sex          | ---                          | Parameter of Interest (CI) |

*General approach to analysis:* For binary outcomes such as anemia status, the parameter of interest is typically the measure of association, such as odds ratio or relative risk. For models with other types of outcome, the parameter is the beta coefficient estimator from the corresponding models.

Generalized linear mixed effects models will be used to analyze the year 5 outcome. A generalized linear mixed effects model was chosen to account for random effects at the village level in year 5 comparison. The unadjusted model is a between-arm comparison without adjustment for other covariates. The adjusted model proposed here only includes adjustment for age and sex.

Generalized mixed effects models with normal, binomial, and multinomial distributional assumptions will be applied to address outcomes that are continuous, dichotomous, or categorical, respectively. SAS code examples for unadjusted models are provided below:

Sample code:

Linear mixed effects model code example

```
proc mixed;
  where Study_Year=5;
  class Person_ID Village_ID Study_Arm;
  model y = Study_Arm / solution;

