class Person_ID Village_ID Study_Arm Study_Year(ref='1');
model y=Study_Year Study_Arm Study_Arm*Study_Year/solution;
random intercept /subject=Village_ID;
random intercept /subject=Person_ID(Village_ID);
run;
```

For binary variables

```
proc glimmix;
class Person_ID Village_ID Study_Arm Study_Year(ref='1');
model y=Study_Year Study_Arm Study_Arm*Study_Year/dist=binomial solution or;
random intercept /subject=Village_ID;
random intercept /subject=Person_ID(Village_ID);
run;
```

For ordinal outcomes

```
proc glimmix;
class Person_ID Village_ID Study_Arm Study_Year(ref='1') y;
model y=Study_Year Study_Arm Study_Arm*Study_Year/dist=multinomial solution;
random intercept /subject=Village_ID;
random intercept /subject=Person_ID(Village_ID);
run;
```

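### The cohort Year 5 morbidity models (Tables 4) leave out each child's own pre-treatment Year 1 value, which can cost precision and let the two primary answers diverge

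*Combined protocol and SAP*

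**What the plan says.** Main SAP, section VII.a, makes the Year 5 comparison a primary question: "1a. Do morbidity markers among cohort children at Year 5 differ by study arm". Section VII.b, Tables 4, sets out its models. All three code examples keep Year 5 records only ("where Study_Year=5") and fit arm with a village random intercept. For the first column, "The unadjusted model is a between-arm comparison without adjustment for other covariates". For the second, "The adjusted model proposed here only includes adjustment for age and sex". The Table 4A shell accordingly has rows for arm, age and sex only.

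The baseline value exists. Section III.b says of the morbidity markers: "The following were measured in Years 1, 3, and 5, except for ultrasound, which was to be conducted in Years 1 and 5". Section I adds that "Y1 data collection is defined as the baseline data collection, which occurs before treatment". The same children are followed throughout.

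Baseline is used in Tables 5, which answer question 1b on change by arm, through the arm-by-year term: "model y=Study_Year Study_Arm Study_Arm*Study_Year/solution". Table 3 also describes every marker by arm at Year 1. On size, section II.d says "Cohort studies aimed to enroll 100 children from at least 4 communities/villages in each study arm".

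**The concern.** A child's earlier value of the same marker is usually among the best available predictors of the later one, and here it costs nothing to obtain. Leaving it out of the Year 5 model gives up whatever precision it would bring, in a sub-study with few clusters.

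Few clusters also make a visible Year 1 difference between arms likely by chance. Part of such a difference persists to Year 5 and stays in the Tables 4 estimate. Tables 5 remove it by subtracting the whole Year 1 difference, which is too much when the correlation is below 1. In a trial with a realized imbalance, the two primary analyses are therefore pulled in opposite directions. They can disagree for no treatment reason, and the SAP does not say which to rely on.

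**Working it through.** **Plan's own figure.** Section II.d: 100 children × 4 villages × 2 arms = 800, as stated. The plan gives no alpha, effect size, SD, ICC, correlation or power for the cohort, so no power figure can be reproduced.

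**Assumptions (not in the documents).** k = 4 villages per arm (the stated minimum), m = 100 children per village, outcome SD 1 at both years, ICC 0.02–0.10, Year 1–Year 5 correlation r = 0.3–0.7, two-sided 5% test on village-level variation with 2 × 4 − 2 = 6 df.

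**Chance Year 1 difference between arms.** SD = √[(2/k)(ICC + (1 − ICC)/m)].
- ICC 0.02: √(0.5 × 0.0298) = 0.12; probability of exceeding 0.2 SD, 10%
- ICC 0.05: √(0.5 × 0.0595) = 0.17; 25%
- ICC 0.10: √(0.5 × 0.1090) = 0.23; 39%

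**Variance relative to the Year 5-only estimate**, with r equal at child and village level: baseline-adjusted 1 − r²; change contrast 2(1 − r). Power is from the noncentral t, with the effect set to give 80% at 6 df unadjusted (noncentrality 3.37, divided by the square root of the relative variance).

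| r | Adjusted variance | Change variance | Power adjusted, 6 df | Power adjusted, 5 df | Power change, 6 df |
|---|---|---|---|---|---|
| 0.3 | 0.91 | 1.40 | 83.5% | 80.3% | 66.2% |
| 0.5 | 0.75 | 1.00 | 89.6% | 87.0% | 80.0% |
| 0.7 | 0.51 | 0.60 | 97.3% | 96.0% | 94.8% |

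The 5 df column gives up one cluster degree of freedom to the covariate. The adjusted variance is (1 + r)/2 of the change variance, so at a common r Tables 5 do not recover the precision. At ICC 0.05 the SE falls from 0.172 SD to 0.165, 0.149 or 0.123 SD.

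**Realized imbalance.** In simulated 4 v 4 trials (ICC 0.05, r = 0.5), among those with a Year 1 difference above 0.2 SD, the mean carry-over in the direction of that difference was about +0.15 SD for Year 5 only, about 0 with baseline adjustment, and −0.14 SD for the change contrast.

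**When village and child correlations differ.** At ICC 0.05 the village component is 0.05/0.0595 = 84% of the variance, so the village-level correlation R matters most. With child-level r = 0.5 and a slope estimated mainly within villages, the relative variance is [0.05(1.25 − R) + 0.0095 × 0.75]/0.0595.
- R = 0.5: 0.75, power 89.6%
- R = 0.3: 0.92, power 83.2%
- R = 0.2: 1.00, power 79.9%, so no gain
- R = 0: 1.17, power 73.7% (about 72–74% with simulated values included)

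**The case against.** The strongest reply is that baseline is already used. Question 1b is also primary, Tables 5 bring in each child's Year 1 value for every marker, and Table 3 displays any imbalance. A reader might infer that the cohort plan ignores baseline altogether. The documents do not support that; the gap is confined to Tables 4 and question 1a. But Tables 5 answer a different question, and at a common correlation their contrast is the less precise one.

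A reader might also infer that the Tables 4 comparison is biased. It is not: chance imbalance averages to zero under randomization, and the village random intercept already carries between-village variation into the standard error. The opposite pulls on Tables 4 and 5 arise only conditional on a realized imbalance.

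Three further points stand. Four villages per arm is a minimum; with 8 per arm the imbalance SD at ICC 0.05 falls from 0.17 to 0.12. The size of any gain rests wholly on assumed correlations, and no document shows that village means at Year 1 predict Year 5 after four years of differing treatment. The arithmetic covers continuous markers only; in the logit models, adding baseline changes the odds ratio to one conditional on baseline.

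The SAP presents itself as a floor and welcomes further analyses, and the cohort protocol, the initial cohort analysis plan and the additional cohort code (Appendices B, J and K) are listed but could not be checked. Neither removes the rule that section VII.b states.

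**Conclusion.** The point holds in limited form. The Year 5 cohort models adjust at most for age and sex and leave out a pre-treatment value of the same marker that was collected on the same children. The consequence is lost precision, and a risk that the two primary answers diverge in a trial with a realized imbalance.

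The size is conditional. At ICC 0.05, 100 children per village, 4 villages per arm and a common correlation of 0.3, 0.5 or 0.7, 80% power becomes about 83%, 90% or 97%, or 80%, 87% or 96% after giving up a cluster degree of freedom. At the low end the gain can therefore be nil. It also disappears at a village-level correlation near 0.2 with child-level 0.5, and turns into a loss below that. It would be wrong to infer that baseline adjustment can never do worse: that is true only when the correlation is the same at both levels and the lost degree of freedom is ignored.

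The change is worth making because the data exist and the cost is low. It should be fixed before results are seen, since adopting it after Tables 4 and 5 disagree would carry little weight.

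**What to change.** In main SAP section VII.b, Tables 4:

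1. Add the child's Year 1 value of the same marker to the adjusted model: `model y = Study_Arm y_Year1 Age Sex`, with the same village random intercept. Add a Year 1 row to the Table 4A shell.
2. Name this as the adjusted estimate interpreted for question 1a, at least for the continuous markers (HAZ, WAZ, BAZ, Hb, VO2, PedsQL). Keep the unadjusted column.
3. For stunting, wasting, anaemia and liver pattern, state that the adjusted odds ratio is conditional on baseline. The gain is then in power rather than a narrower interval, and the figure is not directly comparable with the unadjusted odds ratio. Fall back to the age-sex model if the fit does not converge; the SAP already warns that convergence may be a problem.
4. Keep children who have a Year 5 value but no Year 1 value. Either fill the covariate with the overall Year 1 mean and add a missing indicator, or fit Years 1 and 5 jointly with a common Year 1 mean in both arms. Section VII.c reports PedsQL as 12.7% missing at baseline, and its complete-case rule would otherwise drop these children, so that section needs a matching sentence.

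The cost is SAP wording, one more parameter and a missing-baseline rule, with no new data. Expect little gain, or a small loss, for any marker whose village means at Year 1 do not predict Year 5.

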### c. Missing cohort data

We acknowledge that large numbers of children were lost to follow-up over the five years of the cohort studies. We will not attempt to impute values for them.

Regarding missing outcome data for those included in the cohort, in the primary analyses only children who have all the data needed to assess a particular outcome will be analyzed. In a secondary analysis, multiple imputation and sensitivity analyses will be used to check the robustness of the complete case analysis for outcomes that have 10% or more children without the data needed to conduct the specific analysis. The investigators involved in the Kenya and Tanzania cohorts and SCORE will work together to determine the optimal way to address the missing data issue in their respective datasets.

Preliminary checks on missing data percentages at baseline were conducted for Sm cohort datasets. The missing percentages for major variables were below the 10% threshold, except for PedsQL (12.7%) and some ultrasound variables. Ultrasound variables that are missing in  $\geq 10\%$  of children will not be included in any of the cohort analyses proposed in this SAP. Therefore, we anticipate that the small percentage of the analyses encountering missing data problems can be handled with multiple imputation. SAS programs used to check the missing data percentages are found in Appendix K: 'Additional SAS Code for Analysis of Cohort Data.'

The posterior distribution to be considered should reflect the noise associated with the uncertainty surrounding the parameters of the distribution that generates the data. Sensitivity checks will be conducted to ensure that the multiple imputation methods provide robust estimates. SAS codes and macros will be developed to conduct the multiple imputation and sensitivity analyses with pattern mixture models on the missing data. Some of the SAS programs developed for those purposes have already been included in the Appendix K: 'Additional SAS Code for Analysis of Cohort Data.'

**Table 6. Comparison of imputed and unimputed values for outcomes with  $>10\%$  missing data in Year 5 (from unadjusted models).**

| Outcome | Comparison Arm 1 vs. Arm 6 using raw data
(Complete-Case Analysis) | Comparison Arm 1 vs. Arm 6 using
multiple imputation |
|----------------|-------------------------------------------------------------------------------|-----------------------------------------------------------------|
| Anemia  | Parameter of Interest (CI)                                                    | Parameter of Interest (CI)                                      |
| Weight  | Parameter of Interest (CI)                                                    | Parameter of Interest (CI)                                      |
| ...            |                                                                               |                                                                 |

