  random intercept /subject=Village_ID;
run;
```

Binary outcome code example

```
proc glimmix;
  where Study_Year=5;
  class Person_ID Village_ID Study_Arm;
  model y = Study_Arm / dist=binomial solution or;
  random intercept /subject=Village_ID;
run;
```

Ordinal outcome code example

```
proc glimmix;
  where Study_Year=5;
  class Person_ID Village_ID Study_Arm y;
  model y = Study_Arm / dist=multinomial solution;
  random intercept /subject=Village_ID;
run;
```

Note that convergence could be an issue, and sometimes setting “method=LAPLACE” in the proc line could potentially help with the convergence.

Tables 5 (multiple tables). Comparison between Arm 1 and Arm 6 of change in morbidity outcomes from Year 1-Year 5.

For each outcome, the following type of table should be developed. The results should be as indicated in the cells below.

Example: Table 5A. Comparison of changes in **anemia** rates from Year 1 to Year 5 between Arms 1 and 6.

|                      | Unadjusted                 | Adjusted                   |
|----------------------|----------------------------|----------------------------|
| Arm (1 vs. 6) | Parameter of Interest (CI) | Parameter of Interest (CI) |
| Year          | Parameter of Interest (CI) | Parameter of Interest (CI) |
| Arm*Year      | Parameter of Interest (CI) | Parameter of Interest (CI) |
| Age           | ---                        | Parameter of Interest (CI) |

|     |     |                            |
|-----|-----|----------------------------|
| Sex | --- | Parameter of Interest (CI) |
|-----|-----|----------------------------|

*General approach to analysis:* Generalized linear mixed effect models will be used to analyze the repeatedly measured outcomes from baseline to year 5. The mixed effects model was chosen to account for random effects at the village and individual levels from repeated measures.

Model setups are similar to those from the year 5 comparison (Table 7A), but with random effects from both the “Village\_ID” and “Person\_ID”. Changes from year 1 to year 5 between arms are modeled through the interaction term between “Study\_Year” and “Study\_Arm”. Models with normal, binomial, and multinomial distributional assumptions will be applied to address outcomes that are continuous, dichotomous, or categorical, respectively. SAS code examples for unadjusted models are provided below:

*Sample code:*

Linear mixed effects model code example

```
proc mixed;

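### The cohort SAP concedes heavy loss to follow-up, but no planned analysis examines what that loss does to the Year 5 arm comparison, and the analysis set for the change tables is unclear

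*Combined protocol and SAP*

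**What the plan says.** SAP section II.d sets the cohort size at "100 children from at least 4 communities/villages in each study arm, for a total of 800 children per study". Section III.b has the morbidity markers measured in Years 1, 3 and 5. Ultrasound was planned for Years 1 and 5 only; Kenya added Year 3.

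Section VII.c opens with this acknowledgement: "large numbers of children were lost to follow-up over the five years of the cohort studies. We will not attempt to impute values for them". It then turns to missing outcome data among children in the cohort, for whom "in the primary analyses only children who have all the data needed to assess a particular outcome will be analyzed". The secondary multiple imputation (triggered at 10% missing), the pattern-mixture sensitivity analysis and Table 6 follow from that second statement. After reporting missingness at baseline, the section concludes that "we anticipate that the small percentage of the analyses encountering missing data problems can be handled with multiple imputation".

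For Tables 4 (section VII.b), "Generalized linear mixed effects models will be used to analyze the year 5 outcome", and the sample code filters to Year 5. For Tables 5, "Generalized linear mixed effect models will be used to analyze the repeatedly measured outcomes from baseline to year 5". That code has random intercepts for village and child and no filter on year or completeness. Cohort Table 1 lists, by arm, the baseline characteristics of children lost by Year 5.

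**The concern.** The SAP separates two kinds of missing data: children who left, and items missing in children who remained. It plans a check for the second and none for the first, although it calls the first large. The reassurance in section VII.c rests on baseline percentages, which cannot contain any loss to follow-up.

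Primary question 1a asks whether morbidity at Year 5 differs by arm. A comparison of the children still present answers it only if loss is unrelated to morbidity, or related in the same way in both arms. The two arms deliver treatment differently, community-wide in Arm 1 and school-based with holidays in Arm 6, so equal selection cannot be taken for granted. Earlier measurements on many of the lost children exist and could inform the Year 5 contrast, but Tables 4 do not use them.

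For Tables 5, a team that applies the complete-case sentence would keep only children with both Year 1 and Year 5 data, while a team that runs the code would keep every record. The SAP aims at comparable analysis across countries, so the choice should not be left open.

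**Working it through.** **Planned size.** 100 children x 4 villages x 2 arms = 800, which reproduces the SAP figure. Assumed loss of 20%, 30% or 50% would leave 640, 560 or 400 children for Tables 4. The documents give no attrition rate, effect size or within-child correlation for the cohort, so everything below rests on assumed values.

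**Bias of the Year 5 contrast under no true effect.** Take a continuous marker with SD 1. In one arm, loss follows a logistic model in the Year 1 value with slope b per SD; in the other arm, loss is random. Let d be the shift in the mean Year 1 value among stayers in the first arm:

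d = E[Y1 x P(stay | Y1)] / P(stay)

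With r the correlation between Years 1 and 5:

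- bias of the Year 5 contrast = r x d
- bias of the completer change contrast = (r - 1) x d

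Numerical integration gives d:

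| Slope b | Loss | d |
|---|---|---|
| 0.5 | 30% | -0.143 |
| 0.5 | 50% | -0.236 |
| 1.0 | 50% | -0.413 |

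For the Year 5 contrast:

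- r = 0.36, b = 0.5, 30% lost: 0.36 x (-0.143) = -0.05 SD
- r = 0.5, b = 0.5, 30% lost: 0.5 x (-0.143) = -0.07 SD
- r = 0.5, b = 0.5, 50% lost: 0.5 x (-0.236) = -0.12 SD
- r = 0.6, b = 1.0, 50% lost: 0.6 x (-0.413) = -0.25 SD

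A higher correlation gives more: 0.8 x (-0.413) = -0.33 SD. For loss driven by the Year 3 value, the same formula applies with the Year 3 to Year 5 correlation. Simulation with 400,000 children per arm agrees: -0.074 and -0.117 at r = 0.5, and -0.051 at r = 0.36 with 30% lost.

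**The same contrast from a model on all Year 1, 3 and 5 records** (simulation, village effects omitted):

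| Loss depends on | Year-5-only bias (SD) | All-records Year 5 bias (SD) |
|---|---|---|
| Year 1, one arm, constant correlation 0.5, 30-50% lost | -0.07 to -0.12 | 0.00 |
| Year 1, one arm, decaying correlation (0.6 to 0.36), single child intercept, 30-50% lost | -0.05 to -0.09 | +0.03 to +0.04 |
| Same, unstructured covariance across visits | -0.05 to -0.08 | 0.00 |
| Stable child level, one arm, correlation 0.4-0.6, b 0.5-1.0, 30-50% lost | -0.09 to -0.32 | -0.03 to -0.14 |
| Unseen Year 5 value, opposite by arm, correlation 0.5, b 0.5, 30% lost | -0.28 | -0.20 |

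The all-records contrast is less biased in every row. It is not unbiased when loss depends on something the earlier visits do not capture.

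**Change from Year 1 to Year 5.** Under Year 1-driven loss (r = 0.5, b = 0.5, 30% lost), completer change is biased by (0.5 - 1) x (-0.143) = +0.07 SD and the all-records change by 0.00. Under stable-level loss the order reverses: completer change 0.00, all-records change about -0.03 to -0.14. Neither analysis dominates.

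**The case against.** The strongest reply is that the plan does more than this criticism suggests. The Tables 5 code keeps the Year 1 and Year 3 records of children later lost, so a reader who infers that such children are excluded from all primary analyses goes too far. The complete-case sentence concerns children in the cohort and can be read as item-level only. Cohort Table 1 also reports lost children by arm. All of this stands. What remains is that Tables 4 have no such protection, that Table 1 leads to no analysis, and that the Tables 5 analysis set needs one clarifying sentence.

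A reader might also infer that Tables 4 and 5 will be biased in opposite directions and so contradict each other. The documents do not support that as a property of the plan. It requires loss that depends on baseline differently by arm and Tables 5 cut to completers. Loss driven by Year 3 values leaves completer change unbiased when the correlation is constant, and loss driven by Year 5 values biases both tables the same way.

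The remedy has limits too. Children lost before Year 3 have Year 1 data only, and Year 3 ultrasound exists only in Kenya. The simulations use normal outcomes without village effects. With 4 villages per arm, 280 or 200 children left per arm and an assumed ICC of 0.02 to 0.05, the standard error is sqrt(2 x (ICC/4 + (1 - ICC)/n)): 0.13 SD at ICC 0.02, n = 280, and 0.19 at ICC 0.05, n = 200. The bias at issue is thus of the same order as the sampling error. Appendices B, J and K were not available and may say more. School-leaving as a cause of differential loss is plausible but undocumented; the protocol asks for practical efforts to treat non-attending children.

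**Conclusion.** The concern holds in limited form, as a cheap improvement. The Year 5 cohort comparison rests on stayers, the loss is large by the SAP's own account, and no planned analysis examines its effect on the arm contrast. If loss depends on Year 1 or Year 3 values in one arm only, a bias of about 0.05 to 0.25 SD is plausible at 30-50% loss, slopes of 0.5 to 1.0 per SD and correlations of 0.36 to 0.6. All of these are assumptions, and the true size and direction are unknown.

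For Tables 5 the finding is ambiguity between text and code; exclusion of lost children is not established. Nor may one assume that an all-records model is always safer for change: missing-at-random given earlier visits and the completer-change assumption do not contain each other.

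**What to change.** 1. In section VII.c and under Tables 5, state that the model uses every observed Year 1, 3 and 5 record, including those of children later lost, as the sample code does. Report completer change as a companion.
2. Beside each Year-5-only result in Tables 4, report the Year 5 arm difference from that same model (arm plus arm-by-year). Where it can be fitted, use a covariance across visits that is not limited to a single child intercept. For binary and ordinal outcomes use likelihood-based fitting, such as the LAPLACE option the SAP already mentions.
3. Extend the planned pattern-mixture analysis to lost children, by arm. Keep this separate from the 10% rule that drops ultrasound variables; counting lost children in that rule could remove liver pattern, an outcome of primary interest.

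The cost is a few sentences and some extra model runs, with no new data. The first two steps rely on missing-at-random given the earlier visits, which is why both versions should be shown and the third step is needed.
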